# High-flow nasal cannula versus standard low-flow nasal cannula during deep sedation in patients undergoing radiofrequency atrial fibrillation catheter ablation: a single-centre randomised controlled trial

**DOI:** 10.1186/s13063-022-06362-1

**Published:** 2022-05-09

**Keywords:** Anaesthesiology, Sedation, Deep sedation, High-flow nasal cannula, Atrial fibrillation, Radiofrequency catheter ablation, Randomised controlled trial

## Abstract

**Background:**

To our knowledge, there are few trials studying the effect of high-flow nasal cannula (HFNC) during deep sedation. Our hypothesis is that high-flow nasal cannula (HFNC) will prevent hypoxemia and desaturation as compared to low-flow nasal cannula (LFNC) during prolonged deep sedation in patients with atrial fibrillation undergoing radiofrequency catheter ablation (RFCA).

**Methods:**

A single-centre, randomised controlled trial with HFNC as the intervention and LFNC as the control group. A total of 94 adult patients per group undergoing elective radiofrequency atrial fibrillation catheter ablation under deep sedation. will be included. The primary outcome is the lowest oxygen saturation (SpO_2_). Secondary outcomes are as follows: the duration of lowest SpO_2_, cross over from oxygen therapy in both directions, incidence of SpO_2_ below 90% > 60 seconds, adverse sedation events, adverse effects of HFNC, mean CO_2_, peak CO_2_ and patients experience with oxygen therapy. The study will take place during the 2-day admission period for RFCA. Patients can fill out their questionnaires in the first week after treatment.

**Discussion:**

HFNC is increasingly used as a technique for oxygen delivery in procedural sedation and analgesia. We hypothesise that HFNC is superior to the standard treatment LFNC in patients under deep sedation with respect to the incidence of desaturation. To our knowledge, there are no adequately powered clinical trial studies on the effects of HFNC in prolonged deep sedation.

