In a number of indications, PSA is applied for longer periods. One of these indications is radiofrequency catheter ablation (RFCA) in AF patients with a duration a PSA of more than 3 h. AF ablation has become one of the most common procedures in the electrophysiology lab with rapidly increasing volumes. A recent survey by the European Heart Rhythm Association (EHRA) shows that in 2019, 32% of all procedures are performed under conscious sedation and 27.5% of all procedures under deep sedation [10]. The most commonly used hypnotic drugs were propofol and midazolam, whereas the most commonly used opioids were remifentanil and fentanyl [10]. The potential positive effects of HFNC in this growing patient population is unclear.

In the Maastricht University Centre patients undergoing RFCA are managed by deep sedation with a combination of low dose remifentanil and propofol, as patient movement may result in shifts of the electro-anatomical maps required for the navigation of the ablation catheter and might cause serious complications including air embolisms and cardiac tamponade. Deep sedation is associated with an increased incidence of upper airway collapsibility and disturbed central respiratory drive [13], which results in forced breathing movements during obstructive respiratory events resulting in pronounced intrathoracic pressure swings leading to electro-anatomical map shifts. Additionally, if LFNC is used (standard of care) a sudden drop of oxygen saturation (SpO_2_ < 90%) occurs in 1.5% of patients [17]. Increased pressure in the upper airway during HFNC might reduce upper airway collapsibility during sedation [21] and facilitates active gas exchange during times of hypoventilation [12] allowing stable and long PSA procedures. Additionally, HFNC may enhance carbon dioxide clearance by an entrained and highly turbulent supra-glottic flow vortices created by high-flow nasal oxygen and cardiogenic oscillations [12]**.**

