### Objectives {7}

The aim of this study is to test the hypothesis that oxygen supplementation via HFNC as compared to LFNC can prevent hypoxemia and desaturation in patients with atrial fibrillation undergoing RFCA and prolonged deep sedation of 3 h and more.

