### Outcomes {12}

#### Primary outcome

Primary outcome is the lowest SpO_2_. During PSA continuous SpO_2_ measurements will be recorded using SenTec Digital Monitoring with Vsign 2 sensor. Percentage haemoglobin saturated with oxygen will be measured continuously during the procedures as part of routine clinical practice through the anaesthetic monitoring. SpO_2_ monitoring will be measured by the sensor that is placed on the earlobe and recorded continuously.

Timeframe: The time from the first administration of sedative medication to stopping of the sedative medication (= the end of the procedure).

Measure method: Continuous SpO_2_ measurements will be recorded using SenTec Digital Monitoring with Vsign 2 sensor. SpO_2_ will be measured by the Vsign sensor that is placed on the earlobe and will be recorded continuously.

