### Sample size {14}

The sample size in this prospective study was calculated according to a similar study with the mean lowest SpO_2_ 95.2% (LFNC) and 99.3% (HFNC), with a standard deviation of 0.1 respectively in two different oxygen therapies [28]. Please note that this sample size is, although based on a similar study which compared the HFNC vs LFNC [8], also based on a different indication and with use of shorter (< 75 min) duration of treatment. To achieve 80% statistical power with α error rate of 0.05, the number of patients was calculated to be 94 for each group. An online statistical calculator, Statulator, was used to calculate the sample size for comparing two independent means.

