### Statistical methods

#### Statistical methods for primary and secondary outcomes {20a}

##### Primary outcome

The primary outcome parameter is the lowest SpO_2_. SpO_2_ is a continuous variable and will be presented as mean and standard deviation (SD). Univariable between-group analysis using the independent-samples *t*-test will be performed. To adjust for potentially confounding variables, we will perform multiple linear regression analysis. Covariates will be age, gender, BMI, ASA-classification, duration of RFCA procedure, hypotension and BIS. We will impute missing data using multiple imputation with fully conditional specification. The number of imputations will be set to the percentage of incomplete records. All analyses will be performed according to the intention-to-treat principle. All participants who are randomised are included in the statistical analysis and analysed according to the group originally assigned to, regardless of the treatment received.

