##### Secondary outcomes

Cross over of therapy is a binary categorical variable. We will compare the difference in cross-over between groups using Pearson’s chi-squared test. The analysis of the incidence of hypoxemia is performed either with logistic or Poisson regression depending on the distribution. All continuous variables like area under the curve SpO_2_, ISAS score, mean TcCO_2_ and peak TcCO_2_ will be presented as group mean and SD. Univariable analysis using the independent-samples *t*-test will be performed. Further analysis will be done using multiple linear regression. Covariates will be specified as age, gender, BMI, ASA-classification, duration of RFCA procedure, hypotension and BIS. The occurrence of adverse events will be presented as count and percentage per group. Analysis will be performed using a logistic regression model. Likert type questions will be reported as percentage of patients that scored each of the options, stratified by group. The median for central tendency and frequencies for variability are calculated for analysing these descriptive statistics. The response on the Likert type questions will be analysed separately for each question using the Mann-Whitney *U* test.

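### The hypothesis is about incidence of desaturation, but the trial is sized and tested on mean lowest SpO2, so it cannot support a confirmatory superiority claim on incidence

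*Protocol article*

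**What the plan says.** The Discussion paragraph of the abstract puts the hypothesis in terms of events: "We hypothesise that HFNC is superior to the standard treatment LFNC in patients under deep sedation with respect to the incidence of desaturation". The abstract's Background and Objectives {7} say much the same, the latter that HFNC "can prevent hypoxemia and desaturation in patients with atrial fibrillation undergoing RFCA". The introduction defines hypoxemia as SpO2 below 90%.

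The design is built on a continuous measure. Under Outcomes {12}, "Primary outcome is the lowest SpO_2". In Statistical methods {20a}, "Univariable between-group analysis using the independent-samples *t*-test will be performed", followed by linear regression. Sample size {14} compares two independent means, taking "mean lowest SpO_2_ 95.2% (LFNC) and 99.3% (HFNC), with a standard deviation of 0.1 respectively in two different oxygen therapies", and arrives at 94 per group.

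Incidence of SpO2 below 90% for more than 60 s appears only among the secondary outcomes, and no power is given for it. Its analysis is described as follows: "The analysis of the incidence of hypoxemia is performed either with logistic or Poisson regression depending on the distribution".

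Two event rates are given in Background and rationale {6a}. In the account of ablation under sedation at the centre, with low-flow oxygen (LFNC), "a sudden drop of oxygen saturation (SpO_2_ < 90%) occurs in 1.5% of patients [17". For a general procedural sedation population the figure is 168 per 1000.

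**The concern.** The article poses one question and equips the trial to answer another. A significant difference in mean lowest SpO2 could arise from patients moving within the range above 90%, without fewer of them crossing the threshold. The planning means, 95.2% and 99.3%, are both above it. A reader who takes the abstract at its word could then read a positive primary result as proof that desaturation was prevented. Equally, a non-significant incidence comparison could be read as evidence that it was not. Neither reading would be sound if the trial has little power for incidence.

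A smaller issue is attached. If the observed distribution decides between logistic and Poisson regression, what is estimated (patients with any event, or possibly a number of events) is not settled beforehand. With very few events, one of the two candidate models may also give no usable estimate.

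**Working it through.** **1. The article's own figure.** Inputs from Sample size {14}: means 95.2% and 99.3%, SD 0.1, α 0.05, power 80%. Two-sided testing is my assumption, since the section does not state it.

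n per group = 2(1.960 + 0.842)² / d². On the fraction scale d = (0.993 − 0.952)/0.1 = 0.41, so n = 2 × 7.849 / 0.1681 = 93.4, rounded up to 94. This reproduces the printed number. Treating 0.952 and 0.993 as two proportions gives 249 per group. The 94 therefore comes from a comparison of means and not from one of incidence.

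**2. Events expected at the LFNC rate.** Inputs: 94 per arm; control rate 1.5% (Background and rationale {6a}, no minimum duration). Expected LFNC events: 94 × 0.015 = 1.41. Probability of none: 0.985⁹⁴ = 0.24.

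**3. What significance would take.** Against zero HFNC events:
- Uncorrected chi-square: 3 v 0 gives p = 0.081; 4 v 0 gives p = 0.043.
- Fisher's exact: 5 v 0 gives p = 0.059; 6 v 0 gives p = 0.029.

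The probability of at least 4 LFNC events is 5.3%, and of at least 6 is 0.3%. These are the powers if HFNC removes every event.

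**4. Power across the article's two rates.** The HFNC event rate is not stated, so the values below are assumptions. Exact binomial enumeration, 94 per arm, two-sided 0.05:

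| LFNC v HFNC | Fisher | Chi-square | n per arm for 80% (normal approximation) |
|---|---|---|---|
| 1.5% v 0% | 0.3% | 5.3% | 519 |
| 1.5% v 0.75% | 0.15% | 2.8% | 3,104 |
| 16.8% v 8.4% | 33% | 42% | 244 |
| 16.8% v 5% | 68% | 77% | 109 |

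The article names neither of these tests for incidence. They are used as a conservative and a liberal benchmark.

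The secondary outcome requires more than 60 s below 90%. For a given patient group, its rate can be no higher than that of any drop below 90%.

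**5. Zero events and the logistic model.** At 1.5% v 0.75%, the chance of no events is 0.985⁹⁴ = 0.242 in the LFNC arm and 0.9925⁹⁴ = 0.493 in the HFNC arm. At least one arm is empty with probability 1 − (1 − 0.242)(1 − 0.493) = 0.62. Ordinary logistic regression then has no finite odds ratio. With 1 or 2 events in each arm (1 v 1, 2 v 1, 2 v 2) it converges; the 2 v 1 and 2 v 2 fits have standard errors of the log odds ratio of 1.23 and 1.01, so the estimates are imprecise but exist.

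**The case against.** The outcome hierarchy is consistent: lowest SpO2 is primary throughout, incidence is secondary throughout, and secondary outcomes need not be powered. The superiority statement in Trial design {8} is not tied to incidence. Lowest SpO2 is also the continuous form of the same construct, because a patient's minimum is below 90% exactly when at least one reading was. The area under the 90% threshold, another secondary outcome, bears on hypoxemia too. All this stands. It shows that the fault lies in how the hypothesis is worded and not in the choice of primary outcome.

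The 1.5% is open to question as well. It comes from a cited source that is not at hand and describes a sudden drop, while the article's Discussion reports more desaturation as sedation lengthens. The SD of 10 points that reproduces 94 would, under a normal distribution with mean 95.2, put about 30% of LFNC patients below 90%: Φ((90 − 95.2)/10) = 0.30. A halving from 30.2% to 15.1% would have 65% (Fisher) to 71% (chi-square) power. That is an upper-end illustration, since SpO2 is skewed and no 60 s minimum is applied. So a reader might infer from the 1.5% case that the trial has practically no power for incidence whatever happens; the article's own 16.8% does not support that. The 0.3% figure also belongs to a test that the article does not name.

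A reader might further infer that logistic regression breaks down whenever events are few. Only an empty arm causes that. Nor does naming Poisson regression prove that a count is intended, because it can be fitted to a yes/no outcome. Analysts are blinded, which limits the scope for a favourable choice, but the model still depends on the data.

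**Conclusion.** The mismatch is real and visible within the article: the stated hypothesis concerns events, while the sizing and primary test concern a mean. A confirmatory superiority conclusion on incidence is not supported. Its power is at most about 5% at the article's LFNC rate of 1.5%, 33% to 42% for a halving from 16.8%, and 68% to 77% for 16.8% v 5%. These figures assume 94 analysed per arm, two-sided 0.05 and the HFNC rates shown. They reach 80% in none of the scenarios examined.

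It does not follow that the trial can say nothing about hypoxemia. Incidence can still be estimated, and the primary analysis of lowest SpO2 is not affected by this point. The choice of incidence model is a lesser fault: it is left to the data, and at 1.5% v 0.75% there is about a 62% chance that ordinary logistic regression yields no finite treatment estimate.

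**What to change.** - Restate the hypothesis in the abstract (Background and Discussion) and the aim in Objectives {7} as a difference in mean lowest SpO2 between HFNC and LFNC.
- Describe incidence of SpO2 below 90% for more than 60 s as supportive estimation: patients with at least one event per arm, and the risk difference with an exact 95% confidence interval, without a confirmatory superiority claim.
- In Statistical methods {20a}, replace the choice between logistic and Poisson regression with one prespecified method that tolerates an empty arm, applied to the patient-level yes/no outcome. Fisher's exact test or Firth logistic regression would serve; which of them is a matter of preference.

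The cost is wording and a narrower headline claim. No patients, measurements or procedures are added. If the investigators want incidence to carry the conclusion, it would have to become primary and be sized as such. On the scenarios above that means 109 to 3,104 per arm, depending on the rates assumed.

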**Trial registration:**

ClinicalTrials.gov NCT04842253. Registered on 04 April 2021

## Administrative information

Note: The numbers in curly brackets in this protocol refer to SPIRIT checklist item numbers. The order of the items has been modified to group similar items (see https://nam12.safelinks.protection.outlook.com/?url=http%3A%2F%2Fwww.equator-network.org%2Freporting-guidelines%2Fspirit-2727-statement-defining-standard-protocol-items-for-clinical-trials%2F&data=04%7C01%7C%7Ccebfabce35fe40e5116c08da0ee97648%7C84df9e7fe9f640afb435aaaaaaaaaaaa%7C1%7C0%7C637838693113378492%7CUnknown%7CTWFpbGZsb3d8eyJWIjoiMC4wLjAwMDAiLCJQIjoiV2luMzIiLCJBTiI6Ik1haWwiLCJXVCI6Mn0%3D%7C3000&sdata=aaHdGNuTEzSHq%2FuqF5QPWlcD%2Fk3o7RX5kAxe%2FUb0WIw%3D&reserved=0).

Several randomised controlled trials have been conducted to test the physiological effects of HFNC [5, 8, 9, 19, 26, 28]. The randomised controlled trials were conducted across a variety of critical care populations including patients with acute respiratory failure [8, 19] or after major surgery [9, 28]. However, adequately powered trials of HFNC in patients undergoing PSA are lacking.

Until now, only three small randomised controlled trials of HFNC in patients undergoing PSA have been published. Sago et al. randomised 30 patients undergoing dental surgery into three treatment groups [26]. Patients received a fraction of inspired oxygen concentration of 40% either via HFNC at a rate of 50 l/min and 30 l/min per minute or via a standard nasal cannula at 4 l/min. Participants randomised to the HFNC groups had higher blood oxygen levels recorded than the low-flow group. Participants who received a flow rate higher than 30 l/min under PSA maintained upper airway patency. Douglas et al. randomised 60 participants undergoing bronchoscopy to receive HFNC at 50 l/min with 100% oxygen or to receive 10–15 litres oxygen per minute with a face mask [5]. Desaturation occurred in 4 out of 30 patients allocated to the HFNC group as compared to 10 out of 30 allocated to the standard oxygen group. No statistical difference for the primary outcome (defined as SpO_2_ < 90%) was found between the treatment groups. Riccio et al. included 59 morbidly obese patients undergoing colonoscopy to receive the same fraction of inspired oxygen concentration of 36% either via HFNO at a flow rate of 60 l/min or via nasal cannula at 4 l per minute [24].

No difference in oxygen saturation and the incidence of desaturation periods was reported. From these studies, it can be concluded that HFNC per se did not result in a substantially improved oxygen status. However, it needs to be noted that this conclusion is based on short procedures requiring PSA with a duration of less than 75 min.

In a number of indications, PSA is applied for longer periods. One of these indications is radiofrequency catheter ablation (RFCA) in AF patients with a duration a PSA of more than 3 h. AF ablation has become one of the most common procedures in the electrophysiology lab with rapidly increasing volumes. A recent survey by the European Heart Rhythm Association (EHRA) shows that in 2019, 32% of all procedures are performed under conscious sedation and 27.5% of all procedures under deep sedation [10]. The most commonly used hypnotic drugs were propofol and midazolam, whereas the most commonly used opioids were remifentanil and fentanyl [10]. The potential positive effects of HFNC in this growing patient population is unclear.

In the Maastricht University Centre patients undergoing RFCA are managed by deep sedation with a combination of low dose remifentanil and propofol, as patient movement may result in shifts of the electro-anatomical maps required for the navigation of the ablation catheter and might cause serious complications including air embolisms and cardiac tamponade. Deep sedation is associated with an increased incidence of upper airway collapsibility and disturbed central respiratory drive [13], which results in forced breathing movements during obstructive respiratory events resulting in pronounced intrathoracic pressure swings leading to electro-anatomical map shifts. Additionally, if LFNC is used (standard of care) a sudden drop of oxygen saturation (SpO_2_ < 90%) occurs in 1.5% of patients [17]. Increased pressure in the upper airway during HFNC might reduce upper airway collapsibility during sedation [21] and facilitates active gas exchange during times of hypoventilation [12] allowing stable and long PSA procedures. Additionally, HFNC may enhance carbon dioxide clearance by an entrained and highly turbulent supra-glottic flow vortices created by high-flow nasal oxygen and cardiogenic oscillations [12]**.**

### Objectives {7}

The aim of this study is to test the hypothesis that oxygen supplementation via HFNC as compared to LFNC can prevent hypoxemia and desaturation in patients with atrial fibrillation undergoing RFCA and prolonged deep sedation of 3 h and more.

### Trial design {8}

This study is a single centre, randomised controlled trial and is designed to evaluate the superiority of HFNC compared with LFNC. Based on a power-calculation {14}, it is aimed to include 188 participants. The allocation ratio is 1:1. Patients will be randomised to the intervention group (HFNC during deep sedation) or the control group (LFNC during deep sedation). Figure 1 summarises the study design.

**Fig. 1 Fig1:**
[figure not shown]
Flow diagram of the study design

## Methods: participants, interventions and outcomes

### Study setting {9}

Participants will be recruited at Maastricht University Medical Centre, Maastricht, the Netherlands. Treatment of participants will take place in the same institution.

### Eligibility criteria {10}

#### Inclusion criteria

In order to be eligible to participate in this study, a patient must meet all of the following criteria: Adult (age > 18 years), undergoing an elective RFCA for atrial fibrillation in the MUMC^+^ Cardiac Catheter Labs, under deep sedation administered by a physician assistant (PA) anaesthesiology or nurse anaesthetist (NA)). In this study deep sedation is performed without a protected airway mechanical ventilation.

#### Exclusion criteria

Patients can be excluded of the study if they meet at least one of the following criteria:Age under 18 yearsIncapacitated patientsBody mass index (BMI) > 32 kg/m²Diagnosed sleep apnoea syndrome (SAS)Chronic pulmonary obstructive disease (COPD) gold IV and COPD gold III with frequent or recent exacerbationDiagnosed pulmonary or cardiac condition requiring chronic oxygen therapyComplete nasal obstructionActive nose bleedingUntreated pneumothorax (pre-existing)Recent upper airway surgeryRecent base of skull fractureExpected difficult airwayCOVID infection

##### Who will take informed consent? {26a}

The patient receives a written information letter and is additionally informed about the study. At the catheter ablation outpatient clinic, a physician assistant will obtain the informed consent after preoperative screening. The information about the study is explained and the patient has the opportunity to ask questions about the study. After this, the patient is invited to participate in the study. When the participant gives permission for participation, the informed consent form is signed. Patients will receive a copy.

